## Abstract

**Introduction:**

Stroke often leads to hemiparetic gait, which negatively affects the quality of life and increases socioeconomic burdens. Conventional therapies have limited effectiveness in improving gait. Postural regulation deficits are a key factor contributing to gait disorders. The Gusu Constraint Standing Training (GCST), a novel posture adjustment approach, shows promise in improving central gait disorders. We hypothesize that GCST optimizes gait in hemiparetic stroke patients by enhancing their postural adaptation criticality and improving gait control through the common neural pathways and nodes shared by posture and gait. However, the specific effects and underlying mechanisms of GCST require further study.

**Methods and analysis:**

This multicenter, prospective, sequential study will recruit 180 hemiparetic stroke patients (recovery phase: 3–6 months; chronic phase: ≥6 months post-stroke) across four hospitals, along with 30 healthy controls. GCST is divided into a structured, stepwise intervention (steps A–E) implemented sequentially based on predefined performance criteria. Assessments will be conducted at baseline, after the completion of each intervention step, and at follow-ups. The primary outcome is the minimal knee flexion angle of the hemiparetic limb during the swing phase, quantified using the three-dimensional gait analysis. Secondary outcomes include gait, postural, neuromuscular, and functional measures. Outcome assessors will be blinded to participants’ stroke phase. Longitudinal data will be analyzed using linear mixed-effects models. Healthy controls will provide normative reference values.

**Ethics and dissemination:**

Approved by each hospital’s ethics committees, the study will require informed consent from participants. The results will be shared through academic conferences and peer-reviewed journals while ensuring participant confidentiality.

**Clincial trial registration:**

https://www.chictr.org.cn/showproj.html?proj=235182, Identifier ChiCTR2400094903.

## Introduction

### Background

Stroke presents a significant challenge in global public health, with its incidence rate increasing (1). Approximately 80% of stroke survivors suffer from gait disorders (2), which further increases the socioeconomic burden. Gait disorders are a common sequela of stroke, often leading to secondary injuries such as falls. Restoring normal gait has become a key rehabilitation goal for stroke patients (3).

Regaining normal gait requires restoring the rhythmic control of the Central Pattern Generator (CPG) for gait (4). A number of therapeutic techniques have been designed and applied to improve motor control on the hemiparetic side, including proprioceptive training, orthotic treatment, and functional electrical stimulation (5, 6). However, these techniques are often ineffective in improving gait rhythm, particularly in terms of dynamic knee control in hemiparetic stroke patients (7). Research on targeted and effective treatments is therefore imperative.

Our team’s previous research has shown that adaptive postural training based on ideal postural alignment can enhance dynamic knee control and gait rhythm (8). Given that posture adjustment and walking share common neural pathways and nodes (9), posture adjustment ability may be a promising approach to enhancing gait patterns. Consequently, we developed the Gusu Constraint Standing Training (GCST), which facilitates automatic gait improvement in patients with cerebral palsy and hemiparesis through targeted postural adjustment training (8, 10). By applying quantified perturbation forces, the GCST induces patients to achieve a critical standing point for maintaining standard postural alignment. This process triggers a transition from quantitative changes to qualitative changes, activates lower-extremity motor integration, and enhances patients’ ability to resist external forces from multiple directions (10, 11).

The GCST improves three-dimensional resistance capacity sequentially in the order of the sagittal, coronal, and horizontal planes. The steps were generally found to improve knee control, optimize the gait cycle, and enhance balance and speed. However, the clinical effects, the mechanisms underlying each step, and how their effects vary according to disease duration remain unclear.

### Significance

The GCST shows promise for improving gait in hemiparetic stroke patients in both the recovery phase and the chronic phase. As the first multicenter sequential intervention study on GCST for these patients, this research will systematically evaluate the GCST’s clinical effects and its mechanisms by assessing five levels, including motor integration, spinal reflexes, muscle control, posture and gait, and quality of life. By comparing hemiparetic stroke patients with healthy adults, the study will analyze gait recovery patterns in these patients. The findings will provide new insights and approaches for restoring lower-extremity neuromuscular function in hemiparetic stroke patients, filling significant gaps in this field.

### Objectives

In hemiparetic stroke patients, postural control deficits are associated with central nervous system lesion sites and disease duration. The GCST enhances standing postural adjustment through sequential, plane-specific resistive adaptive modulation, thereby improving postural adaptation criticality (the dynamic capacity of the neuromuscular system to reorganize postural control under external perturbations). This process also modulates brain motor integration and restores the lower-extremity gait rhythm controlled by the CPG.

The objectives are as follows:

To analyze the relationship between postural control deficits and neural damage locations, as well as disease duration, to clarify the specific defects and causes of posture adjustment in hemiparetic stroke patients.To analyze the maximum angles and pulling forces that hemiparetic stroke patients can tolerate in each step and to reveal the adaptive critical state characteristics of postural control.To observe the effects of each GCST step in hemiparetic stroke patients on posture and gait parameters and to systematically assess the clinical efficacy of GCST.To monitor the changes in motor integration in hemiparetic stroke patients by synchronizing multiple muscles of the lower extremities to identify the mechanisms by which GCST optimizes gait patterns through posture adjustment training.

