Given that GCST interventions are implemented in a predetermined sequence, the study does not employ blinding. However, the start and end points of each intervention step are clearly defined by specific tests. The evaluation of treatment efficacy is based on quantitative indicators, which are free from subjective biases. The study adopts a sequential intervention design, allowing patients to commence treatment at a step that matches their functional capabilities and to progress through treatment in a stepwise manner. This approach is advantageous for maximizing the personalized effects of the treatment. To minimize heterogeneity, step skipping is not permitted. All participants are required to complete each step sequentially. Progression is based on predefined functional criteria, and the duration of each step is individually adjusted according to performance. The number of sessions and days required to complete each step are systematically recorded and treated as indicators of intervention exposure.

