**Figure 3 fig3:**
[figure not shown]
Diagram of the GCST steps.

Given that all participants are unilateral hemiparetic, the training commences at step B. Each step utilizes overlapping motor tasks and incremental difficulty to progressively unlock the patients’ potential. Progression from one GCST step to the next is based on predefined performance criteria rather than therapist discretion. Upon passing the step E test, the treatment cycle is concluded. Throughout the treatment, the number of days taken to complete each step is recorded. Each step is implemented at the patient’s maximum tolerable intensity. Once the criteria for progression are met, the next step is initiated immediately. Specific operational details are provided in Figure 2. Intervention sessions are terminated if participants experience dizziness, excessive fatigue (Borg scale > 15), unstable blood pressure, pain exacerbation, or an inability to maintain a safe standing posture. Safety monitoring is performed continuously during training. To ensure treatment fidelity across centers, a standardized intervention manual has been developed. Sessions are documented using structured fidelity checklists. A random 10% of sessions are video recorded (with patient consent) and reviewed by an independent senior investigator. Deviations from the protocol are documented, and corrective feedback is provided.

All hemiparetic stroke patients will receive conventional treatments based on clinical guidelines. They can participate in upper-extremity training, sitting balance exercises, lying-position training, stretching programs, and physical therapy as needed. However, strength training or motor skill training related to standing and gait functions is expressly excluded.

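### Objective 3 seeks the effect of each GCST step, but one fixed sequence with no stroke comparator supports only cumulative change along that sequence

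*Protocol article*

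**What the plan says.** Objectives, third item: "To observe the effects of each GCST step in hemiparetic stroke patients on posture and gait parameters", and then to judge how well GCST works overall. The objective thus has two parts, the individual steps and the programme as a whole. The Background lists what is not yet known: "However, the clinical effects, the mechanisms underlying each step, and how their effects vary according to disease duration remain unclear".

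The design fixes how steps are delivered:

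- **Order.** Study design (text after Figure 2) describes a predetermined sequence and adds "step skipping is not permitted. All participants are required to complete each step sequentially". The Intervention section (text after Figure 3) has all patients begin at step B, so the sequence is B, C, D, E for everyone.
- **Overlap.** Intervention: "Each step utilizes overlapping motor tasks and incremental difficulty to progressively unlock the patients’ potential".
- **No gap.** Intervention: "Once the criteria for progression are met, the next step is initiated immediately".
- **Comparator.** Study design says that no parallel stroke group on standard rehabilitation is included. Healthy controls are assessed once, and conventional treatment continues alongside GCST.
- **Visits.** In the notes to Table 1, t1 to t4 are the assessments at the end of B, C, D and E respectively.
- **Analysis.** The Statistical analysis section plans a mixed model with a time factor whose named levels are before, after and follow-up. Accumulated dose and the length of each step enter as covariates that change over time.

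**The concern.** Under this design, the only evidence on a given step is the change from the visit before it to the visit after it. Because the order never varies, that change has at least four possible sources: the step itself, its position in the sequence, delayed effects of earlier steps, and recovery that would have occurred anyway over the same weeks. The protocol gives reason to take the last source seriously, since Study design ties its stroke-phase windows to time-dependent recovery processes.

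At stake is the step-level part of Objective 3. Even if GCST as a whole works, a pattern of large early and small late increments could be read as information about the steps when it shows only a flattening recovery curve. Study design concedes the missing comparator. It does not say that order and carry-over are tied to step.

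**Working it through.** **The plan's own figure.** The Sample size section gives 174 for one overall paired before-after contrast (dz = 0.1887, one-sided 0.05, power 0.80). The normal approximation is ((1.645 + 0.842)/0.1887)² = 173.6, so 174; the exact noncentral t gives 175. The figure reproduces and is not disputed. It concerns the programme as a whole and says nothing about single steps.

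**Step against period.** Take visits t0 to t4. Let S_B, S_C, S_D and S_E indicate that a step has been completed:

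| Visit | S_B | S_C | S_D | S_E |
|---|---|---|---|---|
| t0 | 0 | 0 | 0 | 0 |
| t1 | 1 | 0 | 0 | 0 |
| t2 | 1 | 1 | 0 | 0 |
| t3 | 1 | 1 | 1 | 0 |
| t4 | 1 | 1 | 1 | 1 |

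The indicator for visit t1 equals S_B − S_C, for t2 it is S_C − S_D, for t3 it is S_D − S_E, and for t4 it is S_E. An intercept, four step effects and four period effects make 9 columns with rank 5. No step effect can be separated from its period.

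**Step against carry-over.** A delayed effect of B that appears one visit later has the pattern 0, 0, 1, 1, 1, which is S_C exactly. Likewise, delayed C coincides with S_D and delayed D with S_E. An intercept, four step effects and three one-step carry-over effects make 8 columns with rank 5. Both rank deficits come from the single sequence, so more patients would not help.

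**Step against linear elapsed time.** If step lengths vary between patients (simulated here for 180 patients with assumed variable durations), an intercept, four step effects and a linear term in elapsed time make 6 columns with rank 6. A strictly linear trend is therefore formally estimable. This rests on two conditions: recovery must be linear, and step length must be unrelated to response. The second conflicts with Study design, which adjusts step length to performance. With sessions of fixed length and weekly frequency (Intervention), accumulated dose largely tracks time on treatment and adds little separate information.

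**Size, as an illustration.** Assume no true difference between steps, recovery proportional to 1 − exp(−t/τ) with τ = 8 weeks, and four steps of equal length L. The documents give neither τ nor L. The increment for the k-th step is exp(−(k−1)L/τ) − exp(−kL/τ), so the ratio of first to last is exp(3L/τ):

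| L (weeks) | 3L/τ | First ÷ last |
|---|---|---|
| 1 | 0.375 | 1.5 |
| 2 | 0.75 | 2.1 |
| 4 | 1.5 | 4.5 |

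At L = 4 the increments are 0.393, 0.239, 0.145 and 0.088 of the theoretical plateau. They sum to 0.865. Dividing each by 0.865 gives about 45%, 28%, 17% and 10% of the gain reached by the end of E.

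**The case against.** The strongest reply is that the protocol claims less than a critic may infer. The verb in Objective 3 is to observe, and describing the state of patients after each stage is legitimate. The same sentence goes on to the efficacy of GCST as a whole, Objective 4 concerns mechanisms of GCST as a whole, and the sample size is for one overall contrast. The remark about mechanisms of each step is background, not an objective. The fixed order is also part of the treatment, since steps are graded by difficulty and gated by criteria. All of this stands, and it makes the point one about wording and interpretation. It does not remove the point, because the objective names the effects of each step and nothing says that increments are conditional on order.

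A reader might infer four stronger things that the documents do not support:

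- **That the trial will rank the steps, or declare one plane effective and another not.** No section says so. The text names three planes and patients receive four steps; no mapping is given in the text, and Figure 3 is not shown.
- **That post-step assessments may fall after the next step has begun, because progression is immediate.** Study design places comprehensive assessments both before and after each step, so the visit after B also serves as the visit before C. No scheduling change is needed on this ground.
- **That no analysis can separate anything.** A linear time trend is formally estimable, as shown above. Period and carry-over are not.
- **That 4.5-fold is an estimate for this trial.** It is one end of an assumed range.

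**Conclusion.** The point holds in a limited form. As written, Objective 3 asks for the effects of individual steps, and the design can deliver only cumulative change along one fixed sequence. The inseparability of step from period and carry-over is exact and rests on no numerical assumption. The planned covariates could remove at most a linear time trend, and only if performance-driven durations are treated as unrelated to response.

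The possible distortion, a factor of about 1.5 to 4.5 between first and last step, is illustrative. It depends on an assumed exponential curve, an 8-week time constant and equal steps of 1 to 4 weeks. The point does not touch the sample size or the order in which treatment is given, and it does not decide whether GCST as a whole is effective.

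**What to change.** Restate the step-level part of Objective 3 as the cumulative change in posture and gait parameters from baseline to the end of B, B+C, B+C+D and B+C+D+E. Add two sentences. The first should say that the increment between consecutive visits is conditional on all earlier steps having been given in this order, and also reflects elapsed time. The second should say that the trial will not attribute an effect or a mechanism to a single step.

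This changes wording only. Visits, sample size and treatment delivery stay as they are. The cost is a narrower claim. If a step-specific claim is essential, it would need a different design, such as a randomised order, a randomised start or stop of steps, or a concurrent control.

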## Methods and analysis

### Study design

This multicenter, prospective, interventional sequential study is led by the Affiliated Suzhou Hospital of Nanjing Medical University. Physicians will recruit hemiparetic stroke inpatients in the recovery phase and the chronic phase from four hospitals in Suzhou—The Affiliated Suzhou Hospital of Nanjing Medical University, The Affiliated Kunshan Hospital of Jiangsu University, The Affiliated Changshu Hospital of Soochow University, and The Gangcheng Rehabilitation Hospital of Zhangjiagang—and 30 healthy adults through the hospitals’ official media. Recruitment is scheduled to begin in October 2025 and will be completed by March 2026. Each participant will be followed for 12 months, so data collection, including follow-up, will conclude in March 2027. Data cleaning and statistical analysis will be conducted from April to June 2027, with primary results expected by July 2027. The study adheres to the SPIRIT guidelines to guarantee high-quality research (12), with the SPIRIT schedule presented in Figure 1 and the specific process illustrated in Figure 2.

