### Assessment and follow-up

Biomechanical assessment equipment is calibrated according to manufacturer guidelines prior to each testing session. Calibration logs are maintained at each center to ensure measurement consistency. Assessments will be conducted at baseline, after the completion of each step, and during semi-annual and annual follow-ups post-treatment. The primary outcome of this study is the minimal knee flexion angle of the hemiparetic limb during the swing phase of gait, measured by three-dimensional gait analysis. This parameter is defined as the lowest knee flexion value observed in the swing phase of each gait cycle and reflects dynamic knee extension control during limb advancement. Reduced knee flexion during swing is a defining biomechanical feature of post-stroke stiff-knee gait and has been consistently associated with impaired toe clearance, altered limb advancement, and compensatory strategies such as hip circumduction and contralateral vaulting (22, 23). From a neuromechanical perspective, insufficient swing-phase knee flexion is linked to abnormal muscle activation patterns, particularly prolonged quadriceps activity and disrupted inter-joint coordination, making this parameter sensitive to lower-limb neuromuscular integration and rehabilitation-induced changes (21, 24) Table 1 presents a detailed schedule of the assessments and the responsible centers.

**Table 1 tab1:** Schedule of assessments and measurement time points.

Timepoint* Assessments^#^	t_0_, t_0*_	t_1_	t_2_	t_3_	t_4_	t_5_	t_6_
MA	√○□	√○□	√○□	√○□	√○□		
sEMG	√	√	√	√	√		
COP	□	□	□	□	□		
PPD	√□	√□	√□	√□	√□		
PS	□	□	□	□	□		
3DGA	√○	√○	√○	√○	√○		
BRS	√○□	√○□	√○□	√○□	√○□		
FMA-LE	√○□	√○□	√○□	√○□	√○□		
FAC	√○□	√○□	√○□	√○□	√○□	√○□	√○□
SLS	√○□	√○□	√○□	√○□	√○□		
BBS	□	□	□	□	□		
MMT	√○□	√○□	√○□	√○□	√○□		
MAS	√○□	√○□	√○□	√○□	√○□		
SF-36	√○□	√○□	√○□	√○□	√○□	√○□	√○□
BI	√○□	√○□	√○□	√○□	√○□	√○□	√○□
TEAE		√○□	√○□	√○□	√○□	√○□	√○□

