Time points: t_0_: Baseline (patients); t_0*_: baseline (healthy controls); t_1−_ t_4_:post-step assessments (after the completion of steps B–E, respectively); t_5_: semi-annual follow-up; t_6_: annual follow-up. MA, muscle architecture; sEMG, surface electromyography; COP, center of pressure; PPD, plantar pressure distribution; PS, postural sway; 3DGA, three-dimensional gait analysis; BRS, Brannstrom recovery stage; FMA-LE, Fugl–Meyer Lower Extremity; FAC, functional ambulation category; SLS, single-leg stance; BBS, Berg Balance Scale; MMT, manual muscle testing; MAS, Modified Ashworth Scale; SF-36, 36-Item Short Form Health Survey; BI, Barthel Index; TEAE, treatment-emergent adverse event; Center indicators: √, Suzhou and Kunshan sites; ○, Changshu site; □, Zhangjiagang site.

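### The March 2027 end of data collection leaves no time for treatment, although the annual follow-up (t6) is placed after treatment

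*Protocol article*

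**What the plan says.** On the calendar, the Study design section says "Recruitment is scheduled to begin in October 2025 and will be completed by March 2026", then "Each participant will be followed for 12 months, so data collection, including follow-up, will conclude in March 2027", and then "Data cleaning and statistical analysis will be conducted from April to June 2027, with primary results expected by July 2027".

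On the visits, the Assessment and follow-up section schedules assessments at baseline, "after the completion of each step, and during semi-annual and annual follow-ups post-treatment". The note to Table 1 labels the last two visits only as "t_5_: semi-annual follow-up; t_6_: annual follow-up", with no starting point for the clock.

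On treatment length, the Study design text after Figure 2 says that "the duration of each step is individually adjusted according to performance". The Intervention text after Figure 3 starts training at step B and ends it by performance: "Upon passing the step E test, the treatment cycle is concluded". The Intervention section gives five 30-minute sessions a week. The text shown gives neither a number of weeks nor a maximum.

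**The concern.** Two stated facts do not fit together. The end date follows only if each patient's 12 months start at enrolment. The visit schedule, read naturally, starts the clock when treatment ends, and four steps of individual length come before that. Nothing in the calendar covers the interval between the two.

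The one-year data are at stake. Table 1 schedules only FAC, SF-36, BI and treatment-emergent adverse events at t6. If visits due after March 2027 were not made, those measures would be missing for patients who enrolled late. Within one enrolment month they would go missing first for patients who took longest to pass the steps. A plain summary of patients seen at t6 would then over-represent fast progressors.

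**Working it through.** **Inputs.** Recruitment runs from October 2025 to March 2026, which is 6 months or 182 days. Follow-up is 12 months, data collection closes in March 2027, and cleaning starts in April 2027 (all from Study design). Planned N is 180 patients (Sample size estimation). Treatment duration D is not stated, so it is treated as an assumption and shown over a range.

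**The plan's own date.** Last enrolment + 12 months = March 2026 + 12 months = March 2027. The stated date is reproduced, but only with D = 0.

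**With t6 counted from the end of treatment.** Last t6 = March 2026 + D + 12 months = March 2027 + D. A patient's t6 falls by 31 March 2027 only if enrolment date + D is no later than 31 March 2026. With even accrual and one D common to all patients, the share past the close is D / 6 for D in months:

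- D = 1 month: 1/6 = 17%, or 30 of 180
- D = 2 months: 2/6 = 33%, or 60 of 180
- D = 3 months: 3/6 = 50%, or 90 of 180

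The same calculation in days, as D / 182:

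| D | Share past close | Of 180 | Last t6 |
|---|---|---|---|
| 4 weeks | 28/182 = 15% | 28 | late April 2027 |
| 8 weeks | 56/182 = 31% | 55 | late May 2027 |
| 12 weeks | 84/182 = 46% | 83 | late June 2027 |
| 16 weeks | 112/182 = 62% | 111 | late July 2027 |
| 24 weeks | 168/182 = 92% | 166 | mid-September 2027 |

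The two sets differ slightly because 4 weeks is shorter than a month. At about 26 weeks every patient's t6 is past the close. The semi-annual visit t5 stays inside the calendar throughout this range.

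**Who is affected first.** Let e be months from the start of recruitment to enrolment. t6 is in time only if e + D is at most 6. For a patient enrolled at the start of January 2026, e = 3, so t6 is late if D exceeds 3 months. At a fixed e, longer treatment decides who is late. The percentages above use one common D, so they measure how many are late and say nothing about the size of any selection.

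**With the clock at enrolment instead.** March 2027 is then correct, but t6 falls 12 − D months after treatment: 11, 10 or 9 months for D = 1, 2 or 3. It is no longer an annual post-treatment visit, and its distance from the end of treatment shrinks as progression slows.

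**Primary outcome.** In Table 1, three-dimensional gait analysis runs from t0 to t4 only, so neither the primary outcome nor the sample size depends on t6.

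**The case against.** **The anchor may be ambiguous rather than wrong.** The phrase "during semi-annual and annual follow-ups post-treatment" could mean half-yearly and yearly visits that merely fall in the post-treatment period, and the Table 1 note does not settle it. Figures 1 and 2 are not shown and may state the anchor. This stands as a limit on certainty. The end-of-treatment reading is still the more natural one, and on either reading one of the two sections needs rewording.

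**A reader might infer that the late t6 data will be lost.** The documents do not say so. The dates are planning dates, and nothing says that visits due after March 2027 will be dropped. A late t6 could simply delay cleaning. Incomplete data follow only if the close is enforced.

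**A reader might also infer that the missing data would be missing not at random and would bias durability upward.** The documents do not support that either. A cut-off of this kind depends on enrolment date and treatment duration. Days and sessions per step are recorded, and the Statistical analysis section enters cumulative dose and step duration as covariates in a likelihood analysis under missing at random. FAC, SF-36 and BI are also measured at t0 to t5. The planned model may therefore account for much of the loss. A raw summary of t6 completers would not have that protection.

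**The scope is narrow.** Only four measures are taken at t6, and one-year durability is not named among the four listed objectives. This stands.

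**Conclusion.** The point holds as an inconsistency between the end date and the visit schedule. On the natural reading, any material treatment time puts the last enrollees' t6 after March 2027. The direction does not depend on how long treatment is, but the size does. About 17%, 33% or 50% of patients would be affected for 1, 2 or 3 months of treatment, assuming even accrual and a common duration; none of these durations is in the documents.

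The consequence is conditional: if the close is enforced, one-year FAC, SF-36, BI and adverse-event data are incomplete, with slow progressors affected first within any enrolment month. Neither actual loss nor a missing-not-at-random mechanism is shown. This should be corrected, but it does not threaten the primary analysis.

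**What to change.** State in Study design, in Assessment and follow-up and in the Table 1 note that t5 and t6 are 6 and 12 months after the end of treatment. Set the end of data collection at 12 months after the last patient's end of treatment, and shift the cleaning and reporting dates to match.

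The cost is a change of text and dates. No patients or procedures are added, but results for the follow-up outcomes come a few months later.

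Counting t5 and t6 from baseline would keep March 2027, but it is not a free alternative. Time since the end of treatment would vary with progression speed, and because treatment has no stated maximum, t5 could fall during training for a slow progressor.
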